#### Development of the Evaluation Plan

##### Study Design

The evaluation of the IHS program is designed as a pilot randomized controlled trial. For recruitment, officially registered preschools in the Provincial Education Department database are stratified according to the socioeconomic status of people living in that area. The three levels of high, middle, and low socioeconomic areas are defined according to the categorization of the Provincial Education Department. Two preschools are randomly selected from each socioeconomic level (a total of 6 centers) and then allocated to the intervention and control groups (Figure 1). Overall, 3 centers in the intervention group (each center belongs to a different socioeconomic level) and 3 centers in the control group are defined. The selected centers are contacted in person and provided with comprehensive information. After confirmation of managers, 2 classes are randomly selected for enrollment (6 classes in the intervention group and 6 classes in the control group). Then, the parents of eligible children are invited in a meeting in preschool, and informed consent is obtained after a brief introduction on the whole program and the role of parents (for parents of the intervention group) and informing parents for data collection and cooperation in filling questionnaires (for parents of the control group). The components of the intervention program for managers, educators, children, and parents are conducted in intervention classes, and control classes receive the conventional preschool education program. Aiming to acknowledge the cooperation of control preschools, the wait-list approach is suggested to the managers to receive the intervention in the next educational year, as well as a comprehensive report for growth, nutrition, and physical activity status of each child, which is given after the intervention, is completed.

The intervention lasts for 6 months. The duration of an educational year in preschools in Iran is the same as elementary schools and lasts for 8 months (October-May). From March 21, there are around 2-week New Year (Norouz) holidays. The intervention will be completed before Norouz holidays. The required data are collected at baseline and after the completion of the intervention period.

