**Intervention**			
	Introduction to managers		1
	Training educators (workshop)		1
	Introduction to parents		1
	Baseline data collection		1
	LEAP activity units every day		1-6
	Providing ongoing support for educators		1-6
	Booster session for educators at month 3		1-6
	Resources and monthly sessions for parents		1-6
	Filling daily logs, weekly reports and comments (increasing intervention efficacy)		1-6
	Postintervention data collection		6
	Feedback from staff and parents		6

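### Centres are allocated before managers agree and parents consent, and parents are informed differently by arm, so consent and the parent-reported baseline are open to knowledge of the arm

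*Protocol article*

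**What the plan says.** The order of steps is in the Protocol article under Study Design.

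- Selection and allocation come first: "Two preschools are randomly selected from each socioeconomic level (a total of 6 centers) and then allocated to the intervention and control groups".
- Contact follows: "The selected centers are contacted in person and provided with comprehensive information".
- Managers then agree and classes are drawn: "After confirmation of managers, 2 classes are randomly selected for enrollment".
- Parents of eligible children are then invited to a meeting at the preschool. In the intervention arm, "informed consent is obtained after a brief introduction on the whole program and the role of parents (for parents of the intervention group". In the control arm, the meeting serves for "informing parents for data collection and cooperation in filling questionnaires (for parents of the control group".

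Participants and Data Collection makes parental consent a condition of entry. In Table 3 the intervention block lists the introduction to managers, the educators' workshop and "Introduction to parents" above "Baseline data collection", all in month 1. The control block starts with baseline.

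**The concern.** Allocating centres at random protects the comparison of children only if the children who enter, and their starting values, do not depend on the allocation. Under the stated order both can.

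**Consent.** The two groups of parents are asked to accept different things. Intervention parents learn of a programme with a role for them; The Intervention section describes a 107-page book and monthly meetings. Control parents are asked to cooperate with measurement. Families willing to accept one request need not resemble families willing to accept the other. Managers, too, decide after their centre has been assigned.

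**Baseline.** A parent who has just heard a talk on a healthy eating and activity programme may describe the child's diet and activity differently from a parent who has not.

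The outcomes are framed as changes (Abstract, Methods), and Data Analysis plans paired tests and analysis of covariance. A baseline shifted in one arm would therefore enter the results. The Discussion names the randomised design as the first strength and intends the evaluation to guide a nationwide programme, so the sequence is likely to be reused.

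**Working it through.** The article states no figure for this point, so the check is mainly one of sequence.

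**1. Allocation against agreement and consent.** Study Design runs: draw two centres per socioeconomic level, allocate, contact, manager agreement, draw classes, parents' meeting, consent. Both agreement and consent follow allocation. No section describes recruitment or baseline assessment carried out without knowledge of the arm.

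**2. Introduction against baseline, for parents.** The programme introduction is part of the consent meeting (Study Design). Entry requires consent (Participants and Data Collection). Hence introduction, then consent, then baseline. This holds whatever the row order of Table 3.

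**3. Workshop against baseline, for educators.** Table 3 puts the workshop row above the baseline row, but both are month 1. Training Educators dates the workshop only as at baseline. The order is suggested, not stated. It matters mainly for the scale on children's attraction to physical activity, for which educators act as interviewers.

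**4. Which measures are exposed.** Diet recall is given by parents (Diet Quality), and home activity comes from a parent questionnaire (Physical Activity Level, Subjective). Weight, height, circumferences and pedometer steps are measured, and so are less open to reporting effects. Selection through consent can touch any outcome.

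**5. How it would enter the analysis.** Let d be the shift in the intervention arm's baseline mean caused by the introduction, s the difference between arms in mean level caused by different families consenting (taken as constant over time), and b the baseline slope if baseline is a covariate.

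| Comparison of arms | Error from d | Error from s |
|---|---|---|
| End values only | 0 | s |
| Change from baseline | −d | 0 |
| Analysis of covariance on baseline | −b·d | (1 − b)·s |

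For b between 0 and 1, none of the three is free of both errors. The documents give neither d nor s, and their signs are unknown.

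**6. What the counts say about uptake.** Inputs: 152 intervention and 148 control children (Data Analysis), 6 classes per arm (Study Design), usually 20 to 30 children per class (Discussion). I assume that the counts are children enrolled.

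- Per class: 152/6 = 25.3 and 148/6 = 24.7.
- Expected children per arm: 6 × 20 = 120 to 6 × 30 = 180.
- If every class held 30: 152/180 = 84% and 148/180 = 82% took part.
- If classes held 25 or 26: participation was nearly complete.

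The counts are thus compatible with high uptake in both arms. They do not show what kind of family declined.

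**The case against.** Much can be said for the plan. Classes are drawn at random and all eligible children in them are invited, so recruiters cannot pick children. The exposure before baseline is one short introduction; the book is read a chapter a month. Consent after allocation is common in cluster designs. Telling control parents about the programme may prompt them to change what they do. Control centres also receive inducements: a later start of the programme is offered to managers, and families get a present, a nutrition consultation and a report on the child. Arm sizes are almost equal. All of this stands, and it limits the likely size. None of it alters the order of steps or makes the information the same in both arms.

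Three stronger readings are tempting and not supported.

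- A reader might infer a bias of definite size, for instance by supposing that 20% or 30% of families declined in the intervention arm alone. That would need 152/0.8 = 190 or 152/0.7 = 217 eligible children, or 31.7 and 36.2 per class. Both lie above the usual range of 20 to 30, even before exclusions for illness or diet.
- A reader might infer that educators were certainly trained before baseline. Only the row order of Table 3 suggests it. The table is not a full chronology: its control block omits the contact with managers and the parents' meeting that Study Design describes.
- A reader might infer that control parents heard of nothing but questionnaires. The text names data collection and questionnaires and does not say that nothing else was told.

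Figure 1 is not available here and might add detail, but the text is clear without it.

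**Conclusion.** The point holds as a weakness in the stated sequence. Allocation precedes managers' agreement and parents' consent, the consent meeting differs by arm, and the intervention arm's baseline follows the programme introduction. Consent and the parent-reported baseline measures are therefore exposed to knowledge of the arm. The educator-assisted scale is exposed as well if the workshop did come first, which the article leaves open.

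The documents show a route for bias, not that bias occurred. Its size and direction cannot be derived, because children eligible, invited and refusing are not given by arm. The conclusion rests on reading the steps in Study Design in the order written. It is worth correcting because the remedy is cheap and a larger programme may inherit the design; it does not by itself invalidate the pilot.

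**What to change.** **For the plan and any later trial**, keep the steps and change their order:

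1. Obtain agreement from the managers of both centres in a socioeconomic pair, then allocate the pair without disclosing the result.
2. Draw the classes.
3. Take consent in both arms with one neutral text that mentions both possible conditions without programme content.
4. Complete baseline.
5. Disclose the allocation, then hold the educators' workshop and the programme introduction for parents.

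The cost is one common consent text and a somewhat later programme start within month 1. How much later depends on the diet recalls: if the 14-day interval (Diet Quality) separates successive recalls, three of them span 2 × 14 = 28 days, so that interval should be clarified. There is also some risk that control parents learn that a programme exists. Leaving programme content out of the text limits this.

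**For the year already run**, which ended by the end of March 2018, the order cannot be changed. Report children eligible, invited and consented by centre and arm; describe baseline as collected after allocation; and state when the workshop took place relative to measurement. Adjust for fixed family characteristics already collected under Sociodemographic Information, such as parental education and income. Do not adjust for parenting habits, which parents reported after the introduction. The cost is one flow table, a few sentences and a few covariates.

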##### Study Setting

Mashhad is a large city in the northeast of Iran and has 7 areas, based on the classification of the Provincial Education Department. Preschools in Mashhad are nonprofit and are under the supervision of the Provincial Education Department. Most of the preschools in Mashhad start at 7:30 am and close at 2:00 pm. This is the official time, but most children, even those whose parents are employed, come at 8:30-9:00 am and leave the preschool at 12:00-12:30 pm. In addition, preschool service taxis follow this time (8:30-12:30). Therefore, children spend around 4 hours at preschools.

**Figure 1 figure1:**
[figure not shown]
Flow diagram of the recruitment process.

##### Participants and Data Collection

In the Iranian preschool bylaws, preschool is not a mandatory level, and all children aged 4-6 years can be registered either in preschool-1 (age, 4-5 years) or preschool-2 (age, 5-6 years). All children aged 4-6 years of the selected classes of each center are included in the study after a valid consent from their parents or legal guardian, while those with known chronic disease, such as cardiovascular, respiratory, endocrine, or musculoskeletal problems—after physician inquiry—as well as those who need to adhere to a specific diet, such as gluten-free or phenylalanine-free diets, are excluded.

Data reflecting the nutrition status, diet quality, physical activity and sedentary behaviors, quality of life, and anthropometry of children, as well as the general sociodemographic status of participants and their families are collected at baseline and after the intervention is completed (Table 3). Data collection is performed by a team of 4 nutritionists who are given comprehensive training to standardize the data collection. They learned how to consistently obtain anthropometric measurements, fill the required questionnaires, and train the use of pedometers and filling the parent-report questionnaires to parents. Data entry is done by one person for consistency (a PhD student). Each preschool takes about 7-10 days to collect all the required data. As parents’ cooperation is very important in the data collection, aiming to acknowledge their cooperation, especially in control preschools, a gift for children and a free nutrition consultation for children and their parents, as well as a comprehensive report for child growth, nutrition, and activity status, are dedicated.

As this is a pilot study and we cannot estimate the attrition rate, there is no need to define the sample size, but sample characteristics represent the population of preschool children in Mashhad.

**Table 3 table3:** Overview of the study process.

Group and action		Months	

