**Conclusions:**

The double burden of malnutrition in early years children is a major health concern in developing countries. This justifies the need for health promotion programs that are specifically designed to target both overnutrition and undernutrition prevention. If the efficacy approved, the IHS could potentially be a comprehensive health promotion program for young children whose lifestyle behaviors can be improved toward a healthy future life in a nutrition transition setting.

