**Control**			
	Baseline data collection		1
	Conventional programs in preschools		1-6
	Final data collection		6

**Table 4 table4:** A list of variables, tools, and data collection points.

Variable	Assessment tool	Timing
Sociodemographic data	Questionnaire	Baseline
Anthropometry (children)	Weight, height, waist and arm circumference, body mass index percentile, and body mass index *z*-scores for age	Baseline/End
Nutrition risk (children)	Nutrition Screening Tool for Every Preschooler	Baseline/End
Food intake and eating habits	24-hour recall×3	Baseline/End
Physical activity level (children)	Children attitude toward physical activity Physical activity level at home Physical activity level by pedometers
Quality of life (children)	Pediatric Quality of Life Inventory questionnaire	Baseline/End
Efficiency and adequacy of the parent material	Interview with parents	End
Feasibility of the program (weaknesses and strengths)	Interview with managers and educators	End

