#### Variables of Interest

Several variables are considered to assess the defined objectives, which are specified earlier. Table 4 presents the main outcome measures that are administered among both intervention and control participants.

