##### Data Analysis

Descriptive analysis (frequency, percentage, mean, and SD) will be used to characterize and compare the basic characteristics of participants in the intervention and control groups. Outcomes related to nutrition and physical activity will be compared between the intervention and control groups to seek any possible improvements following the intervention. Considering the number of intervention (n=152) and control (n=148) participants, which anticipates a normal distribution, independent sample *t* test, and chi-square tests will be used for between-group comparisons, while paired sample *t* test and MacNemar tests will be used for analyzing within-group changes. Any possible covariates will be controlled with the analysis of covariance test. All tests are 2-tailed, and a significance level of <.05 will be considered statistically significant. Data analysis will be done by IBM SPSS Statistics for Windows, version 23.0 (IBM Corp).

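### The pilot label is used to waive any sample-size basis, yet 12 unranked main outcomes are tested at .05 with efficacy in view; the claim that the sample represents Mashhad preschoolers is unsupported

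*Protocol article*

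**What the plan says.** Participants and Data Collection gives the only statement on size: "As this is a pilot study and we cannot estimate the attrition rate, there is no need to define the sample size". The same sentence goes on to say that "sample characteristics represent the population of preschool children in Mashhad".

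The objectives (Textbox 1) include feasibility and attrition. They also ask whether the program can change five areas: physical activity and attraction to it, sedentary behavior at home, anthropometry, quality of life, and eating habits with nutrition risk.

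Variables of Interest gives the outcomes equal rank: "Table 4 presents the main outcome measures that are administered among both intervention and control participants". No primary outcome is named.

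Data Analysis plans between-group t and chi-square tests and within-group paired tests. It reports the achieved numbers as "Considering the number of intervention (n=152) and control (n=148) participants, which anticipates a normal distribution" and adds: "All tests are 2-tailed, and a significance level of <.05 will be considered statistically significant".

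The Abstract's Conclusions read: "If the efficacy approved, the IHS could potentially be a comprehensive health promotion program for young children". The Building Partnership component sends the results to the Ministry with national implementation in mind, and the Discussion sees them as a possible basis for policy.

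**The concern.** The reason given for having no sample size does not work. Attrition is a multiplier applied to a number obtained on other grounds; not knowing it leaves the multiplier open and does not remove the need for a basis. Because attrition is something the study sets out to estimate, the size could have been justified by the precision of that estimate.

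A pilot may properly do without a power calculation if it answers feasibility questions only. The difficulty is the combination: the pilot exemption is taken, and the plan then poses effect questions, ranks no outcome above another, fixes .05 for each test and speaks of efficacy. Read as written, a significant result on any one of many outcomes could be carried to policy makers as evidence that the program works.

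The representativeness statement adds to this, because it invites readers to apply the results to all preschool children in the city.

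**Working it through.** The plan has no sample-size calculation to reproduce. The reported numbers are consistent with the design: 152 + 148 = 300 children; 6 centers × 2 classes = 12 classes; 300/12 = 25 per class, within the 20 to 30 given in the Discussion.

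**Counting the main outcomes.** Only quantitative child outcomes are counted; sociodemographic data and interviews are left out.
- Anthropometry: "Weight, height, waist and arm circumference, body mass index percentile, and body mass index" z-score, which makes 6.
- Activity: "Children attitude toward physical activity Physical activity level at home Physical activity level by pedometers", which makes 3.
- Nutrition risk score (NutriSTEP): 1. Diet quality index from the recalls (YHEI): 1. Quality of life: 1.
- Total: 6 + 3 + 1 + 1 + 1 = 12.

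**False-positive chance, one between-group test each at .05, no true effect.**
- Expected number of false positives: 12 × 0.05 = 0.6, whatever the correlation.
- Independent outcomes: 1 − 0.95^12 = 0.460.
- Common correlation (assumed; simulated with 100,000 draws): 0.40 at 0.3, 0.32 at 0.5, 0.23 at 0.7.
- Only the six anthropometric measures strongly correlated (0.3 to 0.7), all other correlations 0.1: 0.44 to 0.38.
- Counting BMI percentile and BMI z-score as one outcome: 1 − 0.95^11 = 0.43.

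The result is about 23% to 46%, or roughly 5 to 9 times the nominal 5%.

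**Added effect of allocation by preschool.** Centers are allocated, with about 300/6 = 50 children each, but the tests are at child level. The documents give no intracluster correlation (ICC), so 0.01, 0.02 and 0.05 are assumptions. The design effect is 1 + 49 × ICC = 1.49, 1.98, 3.45. The true error of one test is 2 × [1 − Φ(1.96/√design effect)] = 0.108, 0.164, 0.291. For 12 independent outcomes, 1 − (1 − error)^12 = 0.75, 0.88, 0.98. At a common correlation of 0.7 the figures are 0.43, 0.57, 0.83. These show direction only; the 23% to 46% range does not depend on them.

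**A precision basis was possible.** The 95% CI half-width for attrition among 300 children is 1.96 × √[p(1 − p)/300]: 3.4, 4.5 and 5.2 percentage points at assumed attrition of 10%, 20% and 30%. This ignores clustering, which would widen it.

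**Representativeness.** Study Design draws two centers from each socioeconomic level, with no stated link to the size of the level and no stated weighting. Managers and then parents must agree. Children with chronic disease or special diets are excluded, and preschool is not mandatory. Nothing in the article shows that the resulting sample mirrors the city's preschool children.

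**The case against.** The strongest reply is that no rule in the article says one significant result proves efficacy. Data Analysis speaks of looking for possible improvements, which is exploratory language. The Abstract's efficacy sentence is conditional, and the Discussion says the study will guide further development of the program. Multiplicity handling is often left to an analysis plan that is not shown. This stands in part: silence on multiplicity is not the fault here. The fault lies in what the article does fix, namely a waived size, all outcomes main, a .05 threshold and an efficacy frame.

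A reader might infer four stronger things that the documents do not support.
- *A spurious finding is more likely than not.* Multiplicity alone reaches at most 46%. Passing one half needs the clustering effect at an assumed ICC, and even then not in every case.
- *There are 36 efficacy tests (12 between-group and 24 within-group).* Within-group tests describe change in one arm. Children aged 4 to 6 grow over six months, so significance for height or weight within an arm is not a false positive.
- *A real moderate effect would be missed.* With the child-level test as planned, the detectable difference at 80% power is (1.96 + 0.842) × √(1/152 + 1/148) = 0.32 SD. A much larger figure requires both an assumed ICC and a center-level analysis that the plan does not use.
- *The sample is shown to be unrepresentative.* Centers are drawn at random within socioeconomic strata from the official register, and stratum sizes are not given, so disproportion cannot be established.

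**Conclusion.** The point holds as a mismatch between the pilot exemption and the use made of the tests. The reason given for waiving a sample size is not valid, and the plan as written puts the chance of at least one false-positive between-group result at 46% under independence, or about 40% to 23% at assumed common correlations of 0.3 to 0.7, instead of 5%. This rests on 12 outcomes, one between-group test each at two-sided .05, no true effect, and children treated as independent. Testing children while allocating centers raises the risk by an amount that depends on an unknown ICC. The representativeness statement is unsupported; it is not refuted.

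**What to change.** - State that the pilot reports feasibility and attrition with 95% CIs, and between-group effects as exploratory estimates with 95% CIs. Intervals that ignore allocation by preschool will be too narrow.
- State that no outcome is declared effective on p<.05 alone and that a definitive trial is the next step. Reword the efficacy sentence in the Abstract to match.
- If one primary outcome is named, disclose that it was chosen after data collection, since the intervention was complete and analysis had begun when the article was written. Testing all 12 at .05/12 = .0042 would hold the familywise rate at 4.9% only if children were independent, so it does not repair the center-level problem.
- Delete or qualify the representativeness sentence, or weight descriptive estimates by stratum enrollment if the Provincial Education Department can supply it.

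Apart from the optional weighting, these are changes of wording and reporting that need no new data, and they can still be made while analysis is in progress. The price is giving up an efficacy claim that the design cannot support.
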